### Randomisation

When an eligible participant has been recruited and consented, they will be scheduled for randomisation at a later timepoint. AN participants will be individually randomised to one of the two study arms with a 1:1 allocation ratio by a computer-generated allocation sequence using permuted blocks. The block sizes will vary randomly between two and four.

Randomisation lists will have been pre-prepared by a separate researcher who is not involved in participant recruitment. Sealed envelopes will contain the study ID for each participant and the meal assigned to that individual (caloric or non-caloric). When a participant is ready to enter the study, a researcher will draw an envelope and prepare the assigned meal for that participant in the evening for consumption the next morning.

Participants with AN will be admitted to the clinic’s open inpatient unit on the evening prior to study participation to ensure a 12-h overnight fast. On the following day, they will receive the specified interventions and undergo the outlined assessments. Once an AN participant has been randomised and completed the study, a matched healthy control participant will be recruited. Recruitment of healthy control participants will be conducted by study personnel who are masked to the randomisation outcomes of the corresponding AN participant. This approach ensures that the allocation of both AN and healthy control participants remains concealed from recruiting researchers and those conducting assessments. Healthy control participants will undergo the same eligibility assessments as AN participants, be assigned their own study ID and share the same allocation as their corresponding AN participant. However, unlike AN participants, healthy control participants will not be admitted overnight.

Codes will be used to increase information confidentiality and participant anonymity, and participant allocation will be performed based on these codes. Randomisation will continue until *n* 36 AN patients and *n* 36 healthy controls have completed the study as per-protocol participants.

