### Statistical methods

#### Analysis plan

Analysis will be conducted once data collection is complete. No interim analyses will be performed. Initially, the quality and completeness of the data will be assessed. If available, missing values will be entered using information from the individual’s original data file. The dataset will be examined for outliers and inconsistencies. For categorical variables, any responses outside the defined categories will be coded as missing. For continuous variables, values outside the acceptable ranges will also be coded as missing. Missing data will not be imputed.

The analyses will be carried out by the investigators and a biostatistician using the latest version of SPSS Statistics (IBM Corp.), R (R-core team) or equivalent statistical software. For the analysis of functional MRI data, additional software tools described below will be used. Data analysts will be blinded to the participants’ allocation. Significance testing will be two-tailed, and statistical uncertainties will be reported as 95 % confidence intervals. All tests will be conducted with a significance level of 0·05.

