The independent variables of the regression analyses will include (1) type of meal (caloric or non-caloric), (2) AN status (AN or healthy control), (3) AN subtype (restrictive or bulimic type), (4) BMI and (5) duration of AN illness. A random effect for each participant and for each matched set of patient and healthy control will be used to account for within-subject correlations from repeated measurements and dependencies within each matched pair.

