#### Secondary analyses

Secondary outcome variables will be modelled using similar regression models as used in the primary analysis. In these models, time (T_0_/T_1_/T_2_) and the allocation by time interaction will be included as fixed effects, and a random intercept for each subject will be included when analysing variables that are measured at more than two timepoints. Additional parametric tests will be performed as long as the assumptions for them are met. Depending on the type of data, the following statistical methods will be used: Independent *t* test, Pearson *r* and ANOVA. Where necessary, corresponding non-parametric alternatives will be used.

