#### Sample size calculation

A two-tailed power calculation for 70 % power and *P* = 0·05 was performed using G * Power software, for a *t* test with linear regression (two independent groups) and an effect size of d = 0·6, based on results from similar neuroimaging studies^(42)^, determining that thirty-four participants per group (AN/healthy) would be sufficient. To account for potential dropouts or unforeseen issues, thirty-six participants will be recruited for each group to ensure robust statistical analysis.

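### The additional secondary tests are named only in independent-sample form, so any that combine patients with their matched controls ignore the pairing that the primary model accounts for

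*Protocol article*

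**What the plan says.** The Eligibility section matches controls to patients on age, sex and education level. Under Randomisation, patients are individually allocated 1:1, and each control will "share the same allocation as their corresponding AN participant". For any comparison using both groups, the pair is therefore the unit of meal allocation.

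The Primary analysis section accepts the consequence. Its regression has a random effect for each participant and one for each matched set, to account for repeated measurements and "dependencies within each matched pair".

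The Secondary analyses section makes three statements:

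- Secondary outcomes are modelled with regressions similar to the primary one, with time and allocation-by-time terms added. A subject random intercept is specified for variables measured at more than two timepoints. The matched-set effect is not restated.
- Additional parametric tests follow, provided their assumptions are met.
- "Depending on the type of data, the following statistical methods will be used": the independent t test, Pearson r and ANOVA, with non-parametric counterparts where necessary. No paired or pair-adjusted version is named, and the contrasts to be tested are not stated.

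The Analysis plan section sets the error rate for everything: "All tests will be conducted with a significance level of 0·05".

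**The concern.** Two neighbouring sections treat the same participants differently. One models the dependence between a patient and her matched control; the next names tests that assume there is none. The design creates that dependence, so inspecting the data for normality or equal variances does not remove it.

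With positive within-pair correlation, the error runs in opposite directions:

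- **AN against control, and the meal-by-AN interaction.** These are contrasts within pairs. An independent-sample test overstates their standard error and loses power. The interaction is the contrast closest to the hypothesis that calorie-dependent network changes differ between patients and controls.
- **Caloric against non-caloric, pooled over groups.** This is a contrast between pairs. Partners share the arm, so an independent-sample test counts 72 independent observations where there are 36 pairs. It understates the standard error and rejects too often.

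The article does not say which result prevails if an additional test and the regression disagree. Meal-2 consumption is recorded once, at T3, and so does not fit the time terms listed for the secondary models. It could plausibly be analysed with one of the simple tests.

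**Working it through.** **Inputs from the article.** Two-sided testing ("Significance testing will be two-tailed") at 0.05; 36 patients and 36 controls, so 36 pairs; 1:1 allocation, so about 18 pairs per meal; both members of a pair on the same meal. The sample size section has "A two-tailed power calculation for 70 % power" and "an effect size of d = 0·6".

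**Input assumed.** The within-pair correlation ρ of an outcome. The article gives none, so a range is shown.

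**Step 1: the plan's own figure.** For two independent groups, n per group = 2(1.960 + 0.524)²/0.6² = 34.3. That is 34 or 35 depending on rounding; the exact t test needs 36. Power at 34 is 69.6% by the normal approximation and 68.4% by the exact t. The statement that "thirty-four participants per group (AN/healthy) would be sufficient" is therefore reproduced to within two participants. The calculation itself treats the groups as independent.

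**Step 2: true and naive variances.** Let σ² be the outcome variance, n = 36 pairs and m = 18 pairs per arm.

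- AN minus control: true 2σ²(1−ρ)/n; naive 2σ²/n. Naive SE / true SE = 1/√(1−ρ).
- Interaction (difference between arms in the mean pair difference): true 4σ²(1−ρ)/m; naive 4σ²/m. Same ratio, 1/√(1−ρ).
- Pooled meal: true 2 × σ²(1+ρ)/(2m); naive 2 × σ²/(2m). Ratio 1/√(1+ρ).
- Meal within one group: only one member of each pair contributes, so the ratio is 1.

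**Step 3: actual size.** By the normal approximation, size = 2[1 − Φ(1.96 × ratio)]. At ρ = 0.3, for example, AN against control gives 1.96 × 1.195 = 2.34, hence 1.9%; pooled meal gives 1.96 × 0.877 = 1.72, hence 8.6%. A simulation of 40,000 trials with 36 pairs, using t and F tests, gives:

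| Assumed ρ | SE ratio, AN v. control | Size, AN v. control | Size, interaction | SE ratio, pooled meal | Size, pooled meal | Size, meal within AN |
|---|---|---|---|---|---|---|
| 0.05 | 1.03 | 4.5% | 4.3% | 0.98 | 5.8% | 5.0% |
| 0.1 | 1.05 | 3.7% | 4.1% | 0.95 | 6.2% | 5.1% |
| 0.2 | 1.12 | 2.9% | 2.9% | 0.91 | 7.3% | 4.8% |
| 0.3 | 1.20 | 2.0% | 2.0% | 0.88 | 8.8% | 5.0% |

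Simulation error is about ±0.2 points (1.96 × √(0.05 × 0.95/40,000) = 0.0021). The closed form gives 4.4%, 3.9%, 2.8% and 1.9% for AN against control, and 5.6%, 6.2%, 7.4% and 8.6% for pooled meal.

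**Step 4: power.** For AN against control at d = 0.6 with 36 pairs, the paired and independent tests have power of 74% and 72% at ρ = 0.1, 79% and 73% at ρ = 0.2, and 84% and 74% at ρ = 0.3. At ρ = 0 the paired test loses about one point (70% against 71%).

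**The case against.** A reader might infer that the secondary analyses as a whole rest on independent t tests and ANOVA. The text does not support this. Regressions similar to the primary model come first, and on a natural reading the word similar brings the matched-set effect with it. The simple tests are additional.

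They are also conditional on their assumptions, and independence is one of them. Read strictly, that condition excludes these tests wherever patients and their controls are combined. It does not settle the matter, because no alternative is named for that case: the usual non-parametric counterparts, Mann-Whitney and Kruskal-Wallis, assume independence too.

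A reader might also infer that every standard error from these tests would be wrong. That does not follow. The symptom and food-intake hypothesis concerns calorie intake in patients; patients are individually randomised, and a meal comparison within them is valid. The only anti-conservative case, meal pooled over groups, is not a stated hypothesis, and the article does not say that it will be tested this way.

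The size depends on an unknown correlation, which may be small: all participants are female and aged 13–18, and education level probably follows age closely. Nothing in the article supports a value as high as 0.5.

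Nor would a disagreement between a simple test and the regression point only to the error term. The regressions also contain AN subtype, BMI, illness duration and time.

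These objections limit the point to supplementary tests that combine the groups. They do not remove the mismatch with the Primary analysis section.

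**Conclusion.** The point holds in limited form. The main secondary analysis handles the pairing by reference to the primary model, although the article should say so outright. The additional tests are named only in independent-sample form, and any that combine patients with their own controls would use the wrong error term. For an assumed ρ of 0.05 to 0.3, actual size is about 4.5% to 2% for AN against control and for the interaction, and about 5.8% to 8.8% for the pooled meal comparison. At ρ of 0.1 or below, the departure from 5% is roughly one point or less. The figures assume 36 complete pairs split evenly between meals, normal outcomes with equal variance, and positive correlation. Meal comparisons within one group are unaffected.

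**What to change.** In the Secondary analyses section:

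1. State that the matched-set random effect carries over to the secondary models.
2. For any additional test that combines the groups, name the pair-based form:
   - AN against control: paired t test or Wilcoxon signed-rank test on pair differences.
   - Meal-by-AN interaction: pair differences compared between arms.
   - Meal effect pooled over groups: pair means compared between arms.

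   Alternatively, omit these tests and report the corresponding mixed-model contrasts.
3. Keep independent-sample tests for meal comparisons within patients only or within controls only.

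The cost is a sentence or two and no new data. No interim analysis is planned and analysis starts only after data collection, so the change can still be pre-specified. The downside is small: a pair with one member missing drops out of the pair-based tests, so the mixed model should stay the main result.

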#### Dose–response analyses

Additional dose–response analyses will be performed by controlling the previously specified regression models for the amount of mixture consumed in meal-1.

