### Intervention protocol

Depending on their randomisation result, participants will be asked to consume one of two jellies, both composed by a dietitian and prepared by study personnel: one containing 400 kcal and the other calorie-free. Both participants and the person handing out the jelly will be unaware of its caloric content. Participants will be given 15 min to consume the jelly, without forcing them to do so, and the amount consumed will be recorded.

The caloric food used in the study will be prepared using gelatine powder, water, granulated sugar, cinnamon, ginger, turmeric and grated lemon zest. To prepare the mixture, plain gelatine powder and 80 g of granulated sugar are mixed with 100 ml of hot water until a homogeneous consistency is achieved. For flavouring, one teaspoon each of cinnamon, ginger and turmeric, along with the zest of half a lemon, is added. The mixture is then brought to a boil, and after 5 min of boiling, the heat is turned off, and the mixture is left to cool for 15 min. It is then poured into a single-serving container, allowed to cool at room temperature and placed in the refrigerator for 2–3 h to solidify. The final product weighs 250 g.

The ingredients of the calorie-free food are water, agar-agar, two teaspoons of the natural sweetener Stevia, cinnamon, ginger, turmeric, grated lemon zest and lemon juice. As with the preparation of the caloric food, all ingredients are mixed and brought to a boil. After it starts boiling, it is stirred for five more minutes, and once it starts to thicken, the heat is turned off, and the mixture is left to cool for 15 min. The prepared meal is then poured into a single-serving container and refrigerated for 2–3 h until it is ready to be consumed. The final product weighs 250 g.

The ingredients and preparation methods were carefully chosen to ensure that both mixtures have a similar appearance and taste.

Three hours after consuming the first mixture (meal-1), participants will be offered a second meal (meal-2). This meal will always contain calories and consist of a nutritionally balanced, standard oatmeal dish with a distinct taste from the first meal. Participants will be allowed to eat freely, up to a maximum of 500 kcal, to minimise the risk of medical complications such as refeeding syndrome in participants with AN. Participants will have 45 min to complete the meal, and the total amount consumed will be recorded.

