##### Meal-1 and meal-2 food consumption

Although not strictly considered an outcome, the amount of mixture (in grams) consumed in the meal-1 will be recorded and included as a control variable in the analysis. The amount of food consumed in meal-2 will also be recorded by weighing the plate before and after the meal.

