The present study should be assessed with some limitations in mind. First, the analysis plan has purposefully been formulated somewhat loosely, and in so doing, it is not possible to take full advantage of one of the main reasons for methodological pre-specification: to prevent selective outcome reporting. The field of neuroimaging in general and neuroimaging of AN in particular evolves quickly, and it is expected that in 2 years, there will be both new methodological approaches to analysis, particularly new machine learning algorithms, and new neuroimaging studies of AN that need to be considered will have been published. Additionally, we are performing parallel *in vitro* and rodent experiments that will inform the region-of-interest selection and analysis. To enable such translational synergistic effects, it was considered necessary to formulate the analysis plan in this way. All the other purposes of pre-specifying a research strategy are still fulfilled^(70)^, and results will be assessed based on biological feasibility. Second, it is anticipated that some participants with AN will be unwilling to consume the full amount of mixture prepared in meal-1 or to consume meal-2. This may result in reduced contrast between study arms; however, it is not expected to bias the results with type-1 errors. The mixtures were designed to be small enough for ease of consumption yet large enough to produce a metabolic effect and to recruit newly diagnosed patients with AN, which is expected to facilitate the intake, as these individuals are unlikely to have advanced disorders. Third, it is unclear to what extent the masking of participants will be successful, as the approach is still somewhat novel. Even if some unmasking occurs, the study may be able to detect important differences between participants with AN and healthy controls, although the individual effects of psychological and physiological processes will not be fully disentangled. Apart from the participants, all individuals involved in the study are expected to be successfully masked. Finally, the trial evaluates neuroimaging, physiological, subjective and behavioural outcomes with a short follow-up time. Given the limited intervention involved, there is no intention to treat participants, and therefore, no clinical outcomes or hard endpoints are included.

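### The planned dose–response analysis contains no term that measures a dose–response to calories

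*Protocol article*

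**What the plan says.** Under Dose–response analyses the article gives one sentence: "Additional dose–response analyses will be performed by controlling the previously specified regression models for the amount of mixture consumed in meal-1". The outcome section on meal-1 and meal-2 consumption fixes the unit and the role: "the amount of mixture (in grams) consumed in the meal-1 will be recorded and included as a control variable in the analysis".

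The models being extended are given in two places. Under Primary analysis: "The independent variables of the regression analyses will include (1) type of meal (caloric or non-caloric), (2) AN status (AN or healthy control"), followed by AN subtype, BMI and illness duration, with random effects for participant and matched pair. Under Secondary analyses: "time (T_0_/T_1_/T_2_) and the allocation by time interaction will be included as fixed effects". Allocation by time is the only interaction named anywhere.

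The Intervention protocol describes two jellies, "one containing 400 kcal and the other calorie-free", and says of each: "The final product weighs 250 g". Intake is voluntary: "Participants will be given 15 min to consume the jelly, without forcing them to do so, and the amount consumed will be recorded". The Discussion adds that "it is anticipated that some participants with AN will be unwilling to consume the full amount of mixture prepared in meal-1". Under Adherence, a participant who eats 30 % or less of meal-1 counts as non-adherent, so per-protocol intake can range from just above 75 g (0.30 × 250 g) to 250 g.

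**The concern.** The label promises a relation between calories consumed and response. The method adds a single gram slope shared by both jellies. Grams of the calorie-free jelly carry no calories, and each participant chooses how much to eat. The shared slope therefore mixes any calorie effect with the effect of volume and with differences between people who accept more or less food. The quantity that isolates calories is the difference in gram slope between the two jellies, and the model as described omits it.

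This matters because the trial aims to separate metabolic from psychological responses to eating. Its outcomes include hunger, meal anxiety, fear of weight gain and meal-2 intake, all of which could plausibly track how much jelly a patient accepts whatever it contains. The masked calorie-free arm supplies the control slope needed to remove that influence, and this analysis does not use it.

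**Working it through.** **Inputs from the article.** Portion 250 g in both arms; 400 kcal or 0 kcal; 72 participants as 36 matched pairs sharing an allocation, so about 18 per meal-by-status cell; two-sided 5 % level. The article gives no effect size or power for this analysis, so there is no stated figure to reproduce.

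**Step 1: what each coefficient means.** Caloric jelly: 400/250 = 1.6 kcal/g. Calorie-free jelly: 0 kcal/g. Let M = 1 for the caloric meal and G = grams eaten. Suppose the outcome is

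y = a + c·M + s·G + d·(1.6·G·M) + other terms,

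where d is the calorie slope per kcal and s is the volume/selection slope. The planned model has M and G but not G·M. Its G coefficient estimates

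s + 1.6·d·V₁/(V₁ + V₀),

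where V₁ and V₀ are the within-arm variances of G, given the other covariates. With V₁ = V₀ this is s + 0.8·d. It equals the caloric-arm calorie slope (1.6·d) only by coincidence, and it is non-zero whenever s ≠ 0 even if d = 0. The M coefficient is an arm difference at equal intake. Neither is d.

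**Step 2: dilution when calories act (s = 0).** Take d = 0.40 SD per 100 kcal, so the true caloric-arm slope is 0.40 × 1.6 = 0.64 SD per 100 g. The formula gives 0.64/2 = 0.32 for the shared slope; simulation with the article's covariates gave 0.34.

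**Step 3: rejection when calories do nothing (d = 0).** Assumed intake: patients uniform on 30–100 % of the portion, controls on 70–100 %. Assumed link between intake and outcome, equal in both arms, in SD of outcome per SD of grams. Model: meal, AN status and grams by least squares, compared with the same model plus meal × grams.

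| Assumed link | Gram term rejects | Meal × grams rejects |
|---|---|---|
| 0 | about 5 % | about 5 % |
| 0.2 | about 28 % | about 5 % |
| 0.3 | about 55 % | about 5 % |
| 0.4 | about 80 % | about 5 % |

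A separate simulation used change scores and added BMI, subtype and illness duration. A trait such as meal anxiety lowered intake and shifted the change by 0, 0.2, 0.3 or 0.4 SD per SD of trait. The gram term rejected 5 %, 34 %, about 65 % and 89 %; meal × grams rejected 4–5 %. A mixed model with a random intercept per pair agreed (6 % at 0, 68 % at 0.3). With a true slope of −0.2 SD per 100 kcal and an opposing trait effect of 0.3, the gram coefficient had the wrong sign (+0.67 per 100 g) and rejected in 46 % of runs.

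**Step 4: the meal-type term.** In the mixed model, the gram-adjusted meal coefficient rejected in about 4–5 % of runs under the same null. (Least squares that ignored the pairing gave 7–8 %, because both members of a pair share an arm.)

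**Step 5: power of the meal × grams term.** Under the Step 3 intake assumptions, the variance of G is the mean of 175²/12 = 2552 and 75²/12 = 469, plus (212.5 − 162.5)²/4 = 625, giving 2136. The SD is 46 g, or 46 × 1.6 = 74 kcal. A slope of 0.2 SD per SD is thus 0.2/0.74 = 0.27 SD per 100 kcal, and 0.4 is 0.54. Pooled power is about 13 % and 37 %. At 0.7 SD per SD (0.95 SD per 100 kcal) it is about 81 % pooled, but about 56 % in patients alone and 16 % in controls alone. The change-score simulation gave 7 %, 17 % and 33 % at 0.2, 0.4 and 0.6 SD per 100 kcal.

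**Step 6: repeated measures.** Where T₀ is among the modelled timepoints, a gram main effect without grams × time also absorbs differences that existed before anyone ate.

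**The case against.** The strongest reply is that the article never says the gram coefficient will be tested or reported as a calorie effect. It calls grams a control variable, which suggests that the estimate of interest remains meal type, or allocation by time, adjusted for intake. On that reading the test keeps close to its 5 % level (Step 4). This stands: a reader might infer that the plan will produce false calorie findings, and the text does not support that. But the same reading concedes that no dose slope is estimated at all, under a heading that announces one.

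Second, the inflation in Step 3 needs a non-caloric link between intake and the analysed outcome. The primary analysis looks at change from before to after the meal. A stable trait that shifts both scans equally cancels, and the gram term then rejects about 4–5 %. This also stands. On change scores the link must be with the change itself, for example through volume or through an anxiety response to eating. The article makes such a link plausible but does not show it.

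Third, these are additional analyses in a condensed article that calls its own plan deliberately loose, and a product term might appear in a fuller analysis plan. That limits the weight of the point. It does not remove it, because the article does state a method, and that method does not answer the question it is named for.

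**Conclusion.** The point holds as a mismatch between label and model. As described, no coefficient measures a dose–response to calories: meal type is an arm contrast at equal intake, and grams averages slopes at 1.6 and 0 kcal/g. That follows from the article's own figures and needs no simulation.

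The consequences are conditional on the gram coefficient being read as the dose–response. It would then show about half the caloric-jelly slope when calories act, given similar intake spread in the two arms. It would reject about 28/55/80 % of the time when calories do nothing and intake is linked to the outcome or its change at 0.2/0.3/0.4 SD per SD, and 5 % with no link. The intake ranges and the link strengths are assumptions; the article gives neither. The Discussion's expectation that incomplete intake will not cause type-1 errors is reasonable for the arm comparison but does not extend to the gram coefficient. The primary comparison and the sample size are untouched.

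**What to change.** State that the dose–response term is meal type × grams consumed, with both main effects in the model. Equivalently, enter kcal consumed with grams and meal type both retained; kcal alone will not do, because it is nearly the arm indicator. Where measures are repeated, multiply by time and include grams × time. Report the gram slope in the calorie-free arm as the volume/selection slope. Label the analysis exploratory and non-randomised, since amount eaten is chosen after allocation.

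If patients and controls are to be compared, add the further interactions with AN status and say so in advance.

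Cost: no new data. For an outcome with one analysed value per person, such as a change score or meal-2 intake, the pooled version takes one extra term and one degree of freedom; repeated measures or a patient–control comparison take more. The real price is low power for modest slopes (Step 5), lower still within each group, so a null result should not be read as absence of a calorie dose–response. The article says analysis begins only after data collection is complete, so the change can be made beforehand. If the sponsor prefers to keep the present model, the alternative is to rename it an intake-adjusted sensitivity analysis of meal type and drop the dose–response label.
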